## Abstract

**Background:**

For residents of long term care, hospitalisations can cause distress and disruption, and often result in further medical complications. Multi-disciplinary team interventions have been shown to improve the health of Residential Aged Care (RAC) residents, decreasing the need for acute hospitalisation, yet there are few randomised controlled trials of these complex interventions. This paper describes a randomised controlled trial of a structured multi-disciplinary team and gerontology nurse specialist (GNS) intervention aiming to reduce residents’ avoidable hospitalisations.

**Methods/Design:**

This Aged Residential Care Healthcare Utilisation Study (ARCHUS) is a cluster- randomised controlled trial (n = 1700 residents) of a complex multi-disciplinary team intervention in long-term care facilities. Eligible facilities certified for residential care were selected from those identified as at moderate or higher risk of resident potentially avoidable hospitalisations by statistical modelling. The facilities were all located in the Auckland region, New Zealand and were stratified by District Health Board (DHB).

**Intervention:**

The intervention provided a structured GNS intervention including a baseline facility needs assessment, quality indicator benchmarking, a staff education programme and care coordination. Alongside this, three multi-disciplinary team (MDT) meetings were held involving a geriatrician, facility GP, pharmacist, GNS and senior nursing staff.

**Outcomes:**

Hospitalisations are recorded from routinely-collected acute admissions during the 9-month intervention period followed by a 5-month follow-up period. ICD diagnosis codes are used in a pre-specified definition of potentially reducible admissions.

**Discussion:**

This randomised-controlled trial will evaluate a complex intervention to increase early identification and intervention to improve the health of residents of long term care. The results of this trial are expected in early 2013.

**Trial registration:**

Australian New Zealand Clinical Trials Registry: ACTRN 12611000187943

## Background

Older people’s health is increasingly important for New Zealand. Mid-range projections from Statistics New Zealand show the proportion of the population aged 75+ will increase from 5.6% in 2006, to 10.4% by 2031 and 14.7% by 2051. Similar ageing demographics exist throughout the OECD, though New Zealand is still ‘young’ in comparison to most OECD nations. Those over 85 years of age comprised 1.3% of the population in 2001, but used half of residential aged care (RAC) costs
[1]. New Zealand has high rates of use of residential aged care (
[2], in press) with about 70% of residents receiving public funds for their care (Grant Thornton 2010). Healthcare spending will increase markedly with the rise of these ‘oldest old’.

In 2008 a census of older people in residential care was completed in the Auckland region in New Zealand. The findings revealed that 28% of those aged 85+ reside in RAC facilities, and residents were increasingly older and more dependent than previous surveys (2003, 1995, 1989)
[3,4]. The need for residential care does not appear to have diminished even though a number of initiatives including Ageing-in-Place have been implemented
[5]. Those living in residential care facilities are at increased risk of hospitalisation because their physical and mental frailty increases their susceptibility to acute illness and injuries
[6]. Improvements in quality indicators such as urinary tract infections, wounds, and falls are associated with better resident health and decreased hospitalisations
[7,8]. Quality of care depends on the staff, the facility and services available (Schnelle 2004). Residential aged care needs to be ‘better managed’ to improve quality
[9] and reduce costs. ARC staff turnover is high and increasing, with high vacancy rates, particularly for registered nurses and caregivers
[10]. There is a need to develop new ways to support the RAC industry that improve resident outcomes, which in turn possibly reduce avoidable hospitalisations.

Flicker
[9] made recommendations for improving RAC care: an interdisciplinary team approach, and partnering with tertiary institutions and expert groups to develop clinical guidelines to promote best practice. Several resident and facility interventions have been proven to improve health care outcomes
[11]. These include interdisciplinary team medication reviews
[12], nutritional screening and intervention
[13], facilitated end of life advanced care planning
[14] and outreach education and clinical coaching
[15].

Ambulatory sensitive hospitalisations (ASH) are those that are potentially avoidable through early primary care intervention, and include diagnoses such as syncope, congestive heart failure (CHF), constipation, dehydration and volume depletion, fall and hip fracture, influenza, pneumonia and urinary tract infection (UTI)
[16]. In a New Zealand review of interventions specifically to reduce Ambulatory Sensitive Hospitalisations in younger people
[16] reported evidence for successful strategies including: inter-disciplinary, collaborative and patient-centred team approaches, education-based comprehensive care programmes, outreach collaborations by both specialists and generalists for disease-specific interventions and increased access to services for all including the under-served. However residential aged care was not the focus for this review and most reported trials were single-disease based. There is a large gap in the knowledge related to residential aged care transfers to acute hospitals and how best to reduce them. There is a need for detailed examination of available data to better understand why hospitalisations occur in New Zealand settings, in order to intervene rationally.

Evidence supports new models of care in RAC result in reduced hospitalisations. Large scale organisations such as Evercare, a large RCT of Nurse Practitioner input into RAC in the United States, reduced acute hospitalisations
[17] and similar results were reported from Canada
[18]. However the scope of these large scale model changes is often beyond local funding capacity and advanced nursing capability. In addition these studies and their subsequent clinical applications have provided only limited understanding of the types of admissions impacted. It is clear that some admissions are needed for acute and specialist care; however evidence suggests that better preventive care and emphasis on managing acute illness in situ improves resident health outcomes.
[19,20]. Structured RAC interventions have demonstrated success in functional outcomes
[21] and falls
[22], but apart from large scale model change, actual reductions in hospitalisations are not yet proven.

## Methods/design

This is a randomised controlled trial of a complex intervention of a package of supports and services provided by District Health Boards (DHBs) interdisciplinary team outreach to RAC facilities.

The study is taking place in the greater Auckland area of New Zealand. Auckland is the largest metropolitan area of New Zealand with a population of 1.4 million people. Within this region there are 175 aged care facilities, from which the participating facilities were selected on the basis of higher than ‘expected’ hospital admission rates. A total sample size of 1400 resident-years was originally anticipated to provide 80% power (5% significance) to detect a 25% reduction in rate of ASH hospitalisations in the intervention group compared to the control group when an event rate of 60 events per 100 years was expected. However, observed event rate in another cohort after commencement of the trial showed a lower event rate, so power estimates were recalculated. With 18 facilities for each group each with 14 months of follow-up, an average of 38 beds per facility and bed occupancy of 90%, we expect a total of 1500 resident years of follow-up. Revised power is estimated at 53%, considering:

• Inflated sample size as the design effect of 2.0 will allow for moderate intracluster correlation for hospitalisation rates of 0.025
[23,24]

• Rate of 35 ASH admissions per 100 resident years in control facilities vs. 26 ASH admissions in intervention facilities, assuming a Poisson distribution where the mean equals the variance. The control event rate was estimated from re-analysis of the RACIP study (Boyd et al., 2008) and the OPAL study cohort (results not yet published).

However, we anticipate an improvement in power because;

• the facilities were chosen (from statistical modelling) for their higher event rates (e.g. an event rate of 0.40 would provide power of 0.67)

• short-stay residents (under-represented in OPAL-based rates) have a higher event rate

• adjustment for covariates in our analysis will reduce confidence intervals around effect size

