### Analyses

Analysis of primary endpoints will compare rate of ASH admissions between treatment groups followed by other main endpoints. Simple unadjusted rates, relative risks and 95% confidence intervals will be obtained initially, with subsequent multiple regression analysis adjusting for paired randomisation and other variables. Negative binomial regression will be used. Baseline rates will likely be included as a covariate in regression models as pre-intervention hospitalisation rates will be highly predictive of post-intervention rates.

Sub-group analyses to check for effects that differ from the overall treatment effect will be performed for the following:

• facilities classed as charitable, religious or welfare facilities vs. for “for profit” facilities

• for facilities that have only rest-home beds vs. those with both rest-home and hospital beds

• for long-stay vs. short-term (e.g. respite or palliative care) residents

• for facilities providing after-hours primary care cover through either their usual GP or a contracted after-hours primary care provider, vs. those without such cover (effectively using ambulance and emergency department for after-hours primary care)

All main analyses will be formally analysed on an "intention to treat" basis. Tests of significance will be two-tailed. Analysis of secondary outcomes will use standard statistical procedures applicable to categorical, continuous, or failure-time data as appropriate.

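### The revised power of 53% makes no allowance for extra-Poisson variation between residents, so for the same inputs it is optimistic by an amount the protocol does not let one determine

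*Protocol article*

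**What the plan says.** All the power assumptions are in the Protocol article, Methods/design. The original target was 1400 resident-years. After a lower event rate was seen in another cohort, power was recalculated for 18 facilities per arm, 14 months, 38 beds on average and 90% occupancy, giving about 1500 resident-years and 53% power.

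The 53% rests on two stated assumptions:

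- Clustering: a "design effect of 2.0 will allow for moderate intracluster correlation for hospitalisation rates of 0.025".
- Rates and variance: the rates compared are given as "Rate of 35 ASH admissions per 100 resident years in control facilities vs. 26 ASH admissions in intervention facilities". For the spread of the counts around these rates, the calculation proceeds by "assuming a Poisson distribution where the mean equals the variance".

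The section then gives three reasons to expect better power. Facilities were chosen for high rates (a rate of 0.40 is said to give 0.67), "short-stay residents (under-represented in OPAL-based rates) have a higher event rate", and covariate adjustment should narrow the confidence intervals.

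For the comparison itself, the Analyses section says: "Negative binomial regression will be used". It adds that baseline rates will probably be a covariate and that "Tests of significance will be two-tailed".

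**The concern.** Setting the variance equal to the mean treats all residents in a facility as sharing one admission rate. The protocol's own remark on short-stay residents says they do not. When rates differ between residents, some are admitted repeatedly and many not at all, and the variance of the counts exceeds the mean. A negative binomial model allows for that excess; the power calculation does not.

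The design effect could have covered it, but it is tied only to the facility correlation. If that correlation accounts for the whole 2.0, within-facility variation between residents has been set to the Poisson minimum.

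Stated power is already close to one half, and these figures will shape how a null result is read. A reader needs to know which sources of variance they include.

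**Working it through.** **Inputs.** From Methods/design: rates 0.35 and 0.26 per resident-year; 36 facilities; design effect 2.0; correlation 0.025; 5% significance (stated for the original calculation and assumed to carry over). Two-sided testing is from Analyses. The 1700 residents are from the Abstract. Total follow-up is 1500 resident-years as stated, or 36 × 38 × 0.9 × 14/12 = 1436 from the listed components; both are used.

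**Step 1: what the design effect covers.** Design effect = 1 + (m − 1) × 0.025.

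- m = 1500/36 = 41.7 resident-years: 1 + 40.7 × 0.025 = 2.02
- m = 1436/36 = 39.9 resident-years: 1 + 38.9 × 0.025 = 1.97
- m = 38 × 0.9 = 34.2 occupied beds: 1 + 33.2 × 0.025 = 1.83

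On the resident-year basis used for the power, the correlation takes up the whole 2.0.

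**Step 2: reproduce the stated power.** Effective resident-years per arm n = total/2/2.0, which is 359 (1436) or 375 (1500). Power = Φ(z − 1.96).

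- Standard two-rate Poisson, z = 0.09/√((0.35 + 0.26)/n): z = 2.184 and 2.231, power 59% and 61%.
- Control-arm variance in both arms, z = 0.09/√(2 × 0.35/n): z = 2.038 and 2.083, power 53.1% and 54.9%.

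Of the formulas tried, only the second reproduces 53%. At a control rate of 0.40 with the same 26/35 ratio and 1500 resident-years, the standard formula gives 66.5% and the control-variance one 60.5%. So the stated 53% and 67% do not appear to come from one formula, and both starting points are carried forward.

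**Step 3: add variation between residents.** The documents give no dispersion. Assume a resident-level negative binomial variance, mean × (1 + k × mean), with k from 0.5 to 2. Mean admissions per resident = 0.35 × 1500/1700 = 0.31, used for both arms. The combination with the design effect is shown two ways:

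- additive: total inflation 2.0 + 0.31k, so f = (2.0 + 0.31k)/2.0
- multiplicative: total inflation 2.0 × (1 + 0.31k), so f = 1 + 0.31k

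Power = Φ(z/√f − 1.96), with z = 1.96 + 0.075 = 2.035 when starting from the stated 53%.

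| k | f (additive / multiplicative) | from 53%: additive / multiplicative | from 59–61%: additive | from 59–61%: multiplicative |
|---|---|---|---|---|
| 0.5 | 1.08 / 1.15 | 50% / 47% | 56–58% | 53–55% |
| 1 | 1.15 / 1.31 | 47% / 43% | 53–55% | 48–50% |
| 2 | 1.31 / 1.62 | 43% / 36% | 48–50% | 40–42% |

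For the 67% figure, the mean is 0.40 × 1500/1700 = 0.353 and z = 2.400. For k = 0.5 to 2, power is 63% to 54% (additive) or 60% to 45% (multiplicative).

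**Step 4: break-even.** From the standard formula, power drops below 53% only when f exceeds (2.184/2.035)² = 1.15 with 1436 resident-years, or (2.231/2.035)² = 1.20 with 1500. That is k of about 0.5 to 0.65 (multiplicative) or 1.0 to 1.3 (additive).

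**The case against.** A reader might infer that the trial's real power is below 53%, or below one half. The documents do not support that.

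- No dispersion is given, so any k is the reader's assumption. The standard Poisson formula starts at 59% to 61%, and moderate dispersion leaves power at or about 53%.
- The protocol expects offsetting gains. Facilities with higher rates are one. Covariate adjustment is another, with baseline rates described as strongly predictive. As an illustration, the facility component is about 1.0 of the 2.0; if baseline rates explained 31% to 62% of it, they would cancel the additive term for k = 1 to 2 (0.31 to 0.62).
- Planning on Poisson and analysing with negative binomial regression is not in itself a contradiction, because Poisson is the limiting case. The article does not say whether the model is fitted to residents or to facilities. At facility level its dispersion would largely overlap what the design effect already covers.
- It would also be wrong to say that repeat admissions are ignored. Poisson counts allow repeats; what is absent is the excess variance when residents' rates differ. Stay type and care type are recorded or analysed, so part of that difference could be adjusted for.
- Outcome measures says that the first outcome will be calculated as the proportion of residents hospitalised. On that reading repeats would not count at all. This conflicts with its label as a rate and with the power section, and needs reconciling.

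These points stand, and they limit the conclusion to direction for fixed inputs. They do not remove it. Differing rates within a facility inflate the variance of facility totals whichever level is modelled. The gains from higher rates concern the mean, not the variance, and the expected gain from covariates is not quantified.

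**Conclusion.** The point holds in a limited form. The 53% and 67% figures include facility-level clustering and Poisson variation, and nothing for differences between residents within a facility. With the other inputs and the formula fixed, any such variation lowers power, so the figures are optimistic by an amount the documents do not let one determine. For an assumed k of 0.5 to 2, the stated 53% becomes about 50% to 36%, and the standard-formula 59% to 61% becomes about 58% to 40%. These ranges also rest on 1700 residents sharing 1500 resident-years and on the control-arm mean in both arms; averaging the arms gives a mean of 0.27 and a somewhat smaller loss. Whether net power is below 53% is not established.

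**What to change.** In Methods/design, replace the Poisson clause with a negative binomial variance, mean × (1 + k × mean). Estimate k from the two cohorts already re-analysed for the control rate, and say how it is combined with the facility design effect. Restate both power figures from one named formula, with a range for k and the resident-years used (1436 or 1500).

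The cost is one re-run of the power calculation on cohorts already re-analysed. The number of facilities and the planned analysis do not change. The downside is that the stated power may become less favourable.

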### Facility selection

Eligible facilities were all those certified by the DHBs as providing long-term care in the region. Details were obtained of bed numbers and care level provided. Prior to facility recruitment, we examined structural aspects of RAC and evaluated potential associations with avoidable hospitalisations, known as ambulatory sensitive hospitalisations (ASH), taking into account individuals’ demographics and health status. Routine reporting of ASH events in New Zealand ceases at age 75, partly because established classifications of ASH diagnoses are perceived to be ‘less relevant’ for older people, particularly those in RAC. We thus developed an ASH classification based on diagnoses that were relevant for the RAC population. This classification method was used to identify facilities with high hospitalisation rates using multivariate modelling techniques that will be reported separately. Facilities were selected from those identified as at moderate or greater risk of resident hospitalisation based on factors identified during modelling.

### Facility recruitment

Initially facilities were contacted by phone by the project manager and invited to participate in the study. This was followed by a visit to confirm written informed consent and to obtain base-line facility data after which the facility was advised whether allocated to intervention or control. In all, a total of 50 facilities were contacted and invited to participate. Twelve facilities declined to take part, citing work load and the similarity to another study recently undertaken as the main reasons. Two facilities withdrew shortly after randomisation because they did not desire to continue with the research project. These facilities were replaced with two other facilities as the intervention had not begun. One control facility has withdrawn half way through the study as it had changed ownership and the new owners did not want to continue participation in the research. Overall there has been an very positive response to the study as most of the facilities are keen to receive the perceived benefits of the intervention (Figure
1).

**Figure 1 F1:**
[figure not shown]
**Process for recruitment and randomisation of facilities**.

### Randomisation

Thirty-six facilities from three Auckland DHBs were randomised following consent. Facility randomisation was conducted by random number allocation, stratified by DHB and mix of care types (rest home only, or a mix of rest home, dementia and hospital beds). Facility identification was blinded to the main investigators wherever possible (some of the researchers were involved in clinical aspects of the intervention so were required to know only those facilities to which they provided clinical input). The control group were offered the same interventions following the completion of the intervention stage of the study. Control facilities were all blinded to all investigators.

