### Intervention

The intervention builds on aged care programmes already in place in the three Auckland region DHBs. Each DHB has gerontology clinical nurse specialists (GNSs) providing outreach to facilities, but the models of care vary between the DHBs and there is no consistent method to Identify high-risk facilities. The trial intervention delivers outreach tailored to facility needs. The multi-disciplinary team is considered a critical element
[25]. These teams were established at each of the three Auckland DHBs, building on existing RAC outreach services. The team comprises the facility General Medical Practitioner and Nurse Manager, a DHB geriatrician, a DHB Gerontology Nurse Specialist and a community pharmacist that services the facility or DHB clinical pharmacist.

The interventions in this study include:

• Initial baseline facility assessment to identify areas of need and facility care plan

• Benchmarking monitoring resident quality indicators that are linked to the quality of care provided (falls, nutrition, use of restraints, weight loss, UTIs, residents on nine or more medications).

• Three one-hour multi-disciplinary team (MDT) meetings to be held monthly for the first three months at each intervention facility, including medication reviews by the geriatrician in conjunction with the GP, pharmacist and nurse manager. At most, six residents were considered at each meeting with new admissions, those recently hospitalised, and those residents on nine or more medications given priority.

• Gerontology education and clinical coaching for RAC nurses and caregivers including advanced care planning for end-of-life care, nutrition and hydration, early identification of illness, falls prevention, end-stage dementia care, communication with families and practical aspects concerned with resident care.

The intervention continued for nine months with the intensity of the intervention decreasing over time to foster facility independence prior to the conclusion of active involvement, including months 6 and 8 where facilities did not receive any input by the GNSs. The GNSs began the intervention with one new facility per month in order to allow sufficient time for the organisation and delivery of the intervention.

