### Outcome measures

The primary outcome measurements comprise:

 1. Rate of ASH admissions classified using a pre-determined set of ICD codes.

 2. Number of acute admission hospital days.

 3. Number of deaths from any cause, including death in acute hospital or elsewhere obtained from a national mortality database.

Numbers and rates for these three outcomes will be calculated as the proportion of residents hospitalised (1), number of hospital days per occupied bed per year (2) and deaths per person-year (3). Sub-group analyses will be conducted, by age group and gender, and by facility type.

This data will be collected from the date of randomisation to 14 months after the first visit by the GNS in the intervention arm, and for the paired facility in the control arm. Hospitalisation records will be sought five months after the final facility completes its intervention, in order to allow for any delays in registering admissions. Paper reports from each participating facility will enable checking against national records.

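### As written, the control facilities' offer of the programme can open before their 14-month outcome window closes, which would dilute the primary comparison by an unknown amount

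*Protocol article*

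**What the plan says.** Five statements in the protocol article bear on this.

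- **Randomisation**, on the control arm: "The control group were offered the same interventions following the completion of the intervention stage of the study". No month is given, and the offer is tied to a stage of the study.
- **Abstract, Outcomes**: admissions are recorded "during the 9-month intervention period followed by a 5-month follow-up period". Intervention and follow-up are named as two successive periods.
- **Intervention**: "The intervention continued for nine months with the intensity of the intervention decreasing over time". Starts were staggered: "The GNSs began the intervention with one new facility per month". The number of gerontology nurse specialists (GNSs) is not stated.
- **Outcome measures**: data run from randomisation to "14 months after the first visit by the GNS in the intervention arm, and for the paired facility in the control arm". Each control window is thus tied to its pair.
- **Methods/design**, power paragraph: "With 18 facilities for each group each with 14 months of follow-up". All 14 months are counted in both arms.

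The Analyses section makes the main analyses intention to treat. The article does not place the offer after month 14 and does not describe separate handling of control time after the offer.

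**The concern.** If the intervention stage is the 9-month period that the abstract names, its completion comes before the 5-month follow-up, and control facilities may take up the programme while their admissions still count as control events. Under intention to treat that time stays in the control arm. If the programme works, the control rate falls towards the intervention rate and the estimated effect shrinks.

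Uptake is plausible. The Facility recruitment section reports that most facilities were keen to have the programme, and the multidisciplinary meetings fall in its first three months, so even a short overlap could include its most intensive part. The trial already states a revised power of only 53%, and a null result could then not easily be told apart from dilution.

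**Working it through.** **Inputs from the article.** Intervention 9 months, outcome window 14 months, 18 facilities per arm, 1500 resident-years, design effect 2.0, rates of 35 (control) and 26 (intervention) per 100 resident-years, 5% two-sided significance.

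**The plan's own power.** Effective resident-years per arm: n = 1500/2/2.0 = 375. With rates per resident-year, power = Φ[(r₁ − r₂)/√((r₁ + r₂)/n) − 1.96].

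- (0.35 − 0.26)/√(0.61/375) = 0.09/0.0403 = 2.23, so power = Φ(0.27) = 61%.
- The stated 53% is not reproduced. It appears (52.5%) with 36 × 38 × 0.9 = 1231 resident-years, which is 12 months of follow-up, not 14. This is a separate matter; the exposed shares below do not depend on it.

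**Exposed share of control time.**

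1. *Offer at each pair's month 9.* (14 − 9)/14 = 5/14 = 36%. This is the ceiling. Collection starts at randomisation, so the true denominator may be a little over 14 months and the share a little lower.
2. *Offer when the last intervention facility finishes.* Assume three GNSs, each starting one facility a month: 18 facilities start at months s = 0 to 5, three at each. The last finishes at month 5 + 9 = 14. A control whose pair started at s has its window close at month 14 + s.
   - All controls start at month 14: overlap is s months, mean (0+1+2+3+4+5)/6 = 2.5, and 2.5/14 = 18%.
   - Controls rolled out at the same pace, starting at month 14 + r with r = 0 to 5: overlap is max(0, s − r).
     - Same order (r = s): 0.
     - Random order: (5×1 + 4×2 + 3×3 + 2×4 + 1×5)/36 = 35/36 = 0.97 month, or 7%.
     - Reverse order (r = 5 − s): (1 + 3 + 5)/6 = 1.5 months, or 11%.
   - With all controls starting together but other numbers of intervention starts per month, the share is 6% (one), 12% (two) or 29% (six).

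**Effect on the comparison.** Assume that every control takes up the programme and gains the full 35-to-26 effect at once. With c exposed months, the control rate is 0.35 − 0.09 × c/14.

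| Scenario | c (months) | Control rate per 100 | Rate ratio | Power, n = 375 |
|---|---|---|---|---|
| No overlap | 0 | 35.0 | 0.743 | 61% |
| Staggered, random order | 0.97 | 34.4 | 0.756 | 55% |
| Staggered, reverse order | 1.5 | 34.0 | 0.764 | 52% |
| All start when the last facility finishes | 2.5 | 33.4 | 0.779 | 46% |
| All start at pair's month 9 | 5 | 31.8 | 0.818 | 31% |

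On the 1231 resident-years that match the stated power, the worst case goes from 53% to 27%. Half the effect over all 5 months is equivalent to c = 2.5.

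**Cost of cutting every pair at month 9.** n = 375 × 9/14 = 241, so power = Φ[0.09/√(0.61/241) − 1.96] = 43%. That is below the 46% left by half-effect contamination over 5 months.

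**The case against.** The strongest reply is that month 9 is an inference. The Randomisation section speaks of a stage of the study, and with staggered starts that stage most naturally ends when the last facility finishes; Outcome measures uses the same milestone for the data request. A control roll-out as gradual as the first one could then produce no overlap at all. In addition, an offer is not delivery, the programme is phased over nine months so an immediate full effect is unlikely, and a journal article may leave roll-out dates and censoring rules to the full protocol or analysis plan.

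Most of this stands as a limit on size. A reader might infer that 36% of control follow-up was contaminated, or that 18% is a lower bound. The documents support neither: the first needs every control to start at its pair's month 9, the second needs all controls to start together, and no control facility is shown to have started inside its window.

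It does not remove the conflict. The point rests on two stated rules, one tying the offer to the end of the intervention stage and one running control outcomes through a later follow-up. Even on the study-wide reading, the last-started pair finishes its intervention five months before its control's window closes. Overlap is excluded only if the control roll-out happens to be late or ordered enough, or if the intervention stage is taken to include follow-up, contrary to the abstract.

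**Conclusion.** The concern holds as an unresolved conflict of timing: followed as written, the offer can open inside the control outcome window and bias the primary intention-to-treat comparison towards no effect. Whether it did, and by how much, cannot be determined from the article.

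The plausible range for the exposed share is 0 to 36%. The top needs a start at month 9 in every control. Values of 0 to 11% or 18% rest on the assumption of three GNSs and starts over months 0 to 5. The shift in rate ratio from 0.74 to 0.82, and the fall in power from about 61% to 31%, are worst-case figures requiring full uptake and an immediate full effect; realistic losses are smaller.

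It might also be inferred that the primary window should simply be cut short. The arithmetic does not favour that: cutting all pairs at month 9 leaves about 43% power and discards the post-intervention follow-up that the article specifies.

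**What to change.** - Reconcile the abstract, Randomisation and Outcome measures so that the offer to a control facility does not overlap that facility's own 14-month outcome window, and state when the offer opens relative to that window.
- If any control facility has already started, record its start date and keep the 14-month intention-to-treat comparison as primary.
- In that case, pre-specify, before outcome data are analysed, a sensitivity analysis that ends the facility's window at its start date and its paired facility's window at the same elapsed time. A cut-off chosen after seeing the data would be open to selection.

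The cost is a change of wording and a wait of up to 5 months for control facilities. Where facilities have already started, the start dates must be recorded, and the sensitivity analysis has less person-time: at most 5/14 in each affected pair, less if the start came later. The primary analysis loses nothing.
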